**Fig. 2 Fig2:**
[figure not shown]
The location of five specific and five non-specific acupressure points

#### Specific self-administered acupressure

Participants in the specific acupressure group will apply self-administered acupressure on five specific acupressure points including LI4 *Hegu*, GV23 *Shangxing*, BL2 *Zanzhu*, LI20 *Yingxiang* and GB20 *Fengchi*. The acupressure points were selected based on a review of the classical and modern literature [11, 16, 22, 25].

#### Non-specific self-administered acupressure

Participants in the non-specific acupressure group will apply self-administered acupressure on another five non-specific acupressure points which are true acupuncture points on the body but not specifically indicated for AR treatment according to literature including *Extra Luozhen*, GV20 *Baihui*, GB4 *Hanyan*, SI18 *Quanliao* and GB12 *Wangu* [11, 25].

#### Symptomatic relief medications

Participants will be allowed to continue their existing management for AR, such as pharmacological therapy. They will be asked to record the details of all medications used in the medication usage form.

### Outcome measures

Primary and secondary outcome measures will be included in this clinical trial. The comparison between two groups will be at baseline, at the end of the treatment period and at the end of the follow-up period. The RCT schedule of recruitment, interventions and assessments is shown in Fig. 3.

**Fig. 3 Fig3:**
[figure not shown]
The schedule of recruitment, interventions and assessments

#### Primary outcome measures

The primary outcome measure will be AR symptomatic relief measured by a 7-point scale of symptom severity with the score ranging from 1 to 7. It contains four domains including I (nasal symptom severity), II (non-nasal symptom severity) and IV (quality-of-life assessment of rhinitis severity) where a higher score indicates more severe symptoms and better quality of life (QoL) as well as III (global assessment of nasal and non-nasal symptom severity) where a lower score indicates more severe symptoms [23]. The scores of four individual domains will be assessed separately at baseline and during the intervention period on a weekly basis and in the follow-up period on a fortnightly basis. The primary outcome of the intervention will be a combination of the four domains.

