### Sample size

The sample size was calculated using the program G*Power 3.1.9 [20]. Due to the absence of a similar acupressure study, the sample size estimation was based on an acupuncture study [21] that is closest to our study as we feel that using the acupuncture study would produce the best possible estimates of effect size and sample size. The effect size estimate in this acupuncture study was based on the main outcome variable (i.e., total nasal symptom score) which is also used in our study. We have also inflated the estimated sample size to cater for a 10% dropout which normally occurs in studies involving acupuncture. The effect size estimate is 0.6505. To achieve 80% power at the significance level 0.05 we need 45 subjects per group taking into consideration a 10% dropout rate.

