### Data analysis

Statistical analyses will be performed by an independent statistician at RMIT University using IBM SPSS Statistics for Windows Version 25 software (IBM Corp., Armonk, NY, USA). The chi-square test will be used to assess differences between the two treatment groups on categorical variables such as characteristic and demographic data at baseline. The *t* test will be used to assess differences between the two treatment groups on the primary outcomes (nasal and non-nasal symptom scores, QoL, global assessment score as well as the total score of the four domains) and secondary outcome variables (RQLQs and relief medication scores) at the end of treatment and follow-up periods. All analyses will follow the intention-to-treat principle. The Worst-Case-Scenario method will be employed to deal with the missing data. That is, we will carry forward the worst possible outcomes for the missing data. Participants enrolled in the study with data from at least one treatment will be included for analysis. No interim analysis will be performed due to the short duration of the trial.

All comparisons will be two-tailed and *p* values < 0.05 will be considered as statistically significant. Subgroup analysis may be performed according to syndrome differential diagnosis of Chinese medicine, severity of symptoms or age group of participants.

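### The primary total score combines domains described as running in opposite directions, with no alignment stated; summed as described, a true benefit partly cancels

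*Protocol article*

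**What the plan says.** Under Primary outcome measures, symptom relief is "measured by a 7-point scale of symptom severity with the score ranging from 1 to 7". The scale has four domains: I (nasal symptoms), II (non-nasal symptoms), III (global assessment) and IV (quality-of-life assessment of rhinitis severity).

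Domains I, II and IV are described together as those "where a higher score indicates more severe symptoms and better quality of life (QoL) as well as III", and III is then set apart as the domain "where a lower score indicates more severe symptoms". The section ends: "The primary outcome of the intervention will be a combination of the four domains".

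Data analysis lists the primary outcomes for the t test as the nasal and non-nasal symptom scores, QoL, "global assessment score as well as the total score of the four domains". It also says that missing data will be replaced by the worst possible outcome.

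Neither section says that any domain is reverse-scored before the total is formed, or whether a lower or a higher total means improvement.

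**The concern.** A total can be read as severity only if its components point the same way. As described, an effective treatment lowers I and II and raises III, so the movement in III subtracts from the movement in I and II.

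Domain IV cannot be placed from the text. It is grouped with the higher-is-worse domains and named as a severity assessment, yet a higher score is said to mean better quality of life. Taken literally, IV runs with III and against I and II.

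The size, and in the extreme case the presence, of a treatment difference in the primary total then depends on a scoring step that the protocol does not state. If that step is settled only after allocation is revealed, it becomes a post hoc choice about the primary result.

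**Working it through.** **Inputs from the protocol**
- Sample size: "The effect size estimate is 0.6505", an estimate "based on the main outcome variable (i.e., total nasal symptom score" of an acupuncture study. Also: "To achieve 80% power at the significance level 0.05 we need 45 subjects per group taking into consideration a 10% dropout rate".
- Data analysis: two-tailed tests. Randomization and blinding: 1:1 allocation.

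**The plan's own figure.** A two-sided 5% t test with d = 0.6505 and 80% power needs 38.08, so 39 per group. Allowing for 10% dropout, 39/0.9 = 43.3, so 44. The normal approximation gives 38, and 38/0.9 = 42.2, so 43. The stated 45 is reproduced to within two participants.

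**Assumptions for the total (not in the protocol).** The four domains have equal weights, unit SDs, the same true improvement δ and a common correlation ρ when all are coded in the severity direction. The aligned total is assumed to have d = 0.6505. The number analysed is 40 per arm (45 × 0.9 = 40.5, rounded down).

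**Formula.** Let a be the vector of signed weights. The standardised effect of the total is

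d = δ·Σa / √[(1−ρ)·Σa² + ρ·(Σa)²].

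- All aligned, a = (1, 1, 1, 1): the raw difference is 4δ and d = 4δ/√(4+12ρ). Setting this to 0.6505 gives δ = 0.6505·√(4+12ρ)/4. At ρ = 0.5, δ = 0.6505 × 3.162/4 = 0.514.
- III opposed, a = (1, 1, −1, 1): the raw difference is 2δ, half of the aligned value. The variance is 4(1−ρ) + 4ρ = 4, so d = 2δ/2 = δ.
- III and IV opposed, a = (1, 1, −1, −1): the raw difference is 0, so d = 0.

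**Results at 40 per arm**

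| ρ | Aligned: d, power | III opposed: d, power | n per arm for 80% power, III opposed |
|---|---|---|---|
| 0.3 | 0.65, 82% | 0.45, 51% | 80 |
| 0.5 | 0.65, 82% | 0.51, 62% | 61 |
| 0.7 | 0.65, 82% | 0.57, 72% | 49 |
| 0.9 | 0.65, 82% | 0.63, 79% | 42 |

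The aligned total needs 39 per arm. With III and IV both opposed, power equals the 5% significance level at any sample size.

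**Sensitivity to weights (ρ = 0.5, δ = 0.514).** These cases use half weight for the opposed domains.
- III alone opposed: Σa = 2.5 and Σa² = 3.25, so d = 2.5 × 0.514/√(1.625 + 3.125) = 0.59, power 74%.
- III and IV opposed: Σa = 1 and Σa² = 2.5, so d = 0.514/√(1.25 + 0.5) = 0.39, power 40%.

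Complete cancellation is therefore specific to equal weights and effects.

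**Worst-case imputation.** On a 1-7 scale the worst value is 7 for I and II and 1 for III. Those values differ, but they do not conflict. For IV the text supports either 1 or 7. For an unaligned total, no direction is defined as worst.

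**The case against.** Neither section says that raw, unreversed scores are added. Recoding is often set by the instrument's scoring source or by an analysis plan, and neither is shown. The authors themselves point out that III runs the other way, which makes an unthinking raw sum less likely. If recoding is specified elsewhere, no power is lost. This stands, and it makes the loss conditional. It does not clear the text: the article states the directions and the total itself, and its description of IV is contradictory whatever another document says.

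The stronger reading, that a benefit cancels entirely, is not supported. It needs the literal reading of IV together with equal weights and effects. The grouping of IV with I and II, and its name, suggest instead that the word for better may be a slip.

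The power figures are also illustrative. Item counts, weights, SDs and correlations are not given, and 0.6505 comes from a total nasal symptom score, not a four-domain total. At a correlation of 0.9 with III alone opposed, little power is lost.

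A reader might also infer that the trial could not show a benefit at all, or that worst-case imputation fails throughout. Neither follows. Each domain is tested separately and I to III have a stated direction, so a benefit there could be seen and interpreted. The worst value is likewise clear for I to III.

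**Conclusion.** The point holds in conditional form and should be corrected before analysis, because it lies in the definition of the primary outcome. III is described as opposed to I and II, the direction of IV contradicts itself, and the primary total is formed with no alignment stated.

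If the total is summed as described with III alone opposed, the raw treatment difference is halved and power at 40 per arm falls from 82% to about 51-79%. That range assumes equal weights, SDs and effects, correlations of 0.3-0.9, and an aligned effect of 0.6505. If IV is also opposed, the loss is greater, reaching complete cancellation only under equal weights and effects.

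The separate tests of I to III remain interpretable, but they do not repair the combined score named as the primary outcome. The imputation problem is confined to IV and the unaligned total.

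**What to change.** In Primary outcome measures, and in the analysis plan if there is one:

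1. Check the direction of domain IV against the instrument and correct the sentence that describes it.
2. State that every opposed domain (III, and IV if the instrument confirms it) is reverse-scored as 8 minus score on the 1-7 scale before the total is formed, so that higher means worse throughout.
3. State that a lower total then means improvement.
4. State that worst-case imputation is applied in this aligned direction.

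The planned total can otherwise stay as it is; no new weighting scheme is needed.

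The cost is a few sentences and a recode in the analysis program, with no change to data collection or sample size. Trial status reports recruitment still in progress at publication, so at that point the rule could be fixed before allocation was revealed.

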#### Secondary outcome measures

The secondary outcome measures will consist of the RQLQs [24], relief medication scores, adverse events and participants’ opinion about this clinical trial. The RQLQs is used to assess the patient’s quality of life and daily activities which contain seven domains with scores from 0 to 6; a higher score indicates a more severe impact on QoL [24]. The use of anti-allergic medication is calculated as each daily dose of antihistamines or decongestant nasal spray or eye drops was equivalent to 1 point; orally administered antihistamines as 2 points and a steroid nasal spray or eye drops as 3 points [26]. If the participants use orally administered corticosteroids or acupuncture for AR during the trial period, they will be asked to discontinue the self-administered acupressure treatment and considered as withdrawing from this study. Adverse events will be self-monitored and recorded in the adverse events form. If there are severe adverse events from the self-administered acupressure, the relevant participants will be asked to terminate the study and contact the researchers immediately. They will be referred to general practitioners or the emergency department for management. All severe adverse events will be investigated and reported in writing to the RMIT HREC immediately. A questionnaire will be used to seek participants’ opinion on the expectancy of self-administered acupressure for AR and the credibility of the blinding method used in the study.

RQLQs and relief medication scores will be assessed at baseline, intervention period (weekly) and follow-up period (fortnightly). Acupressure dosage and adverse events will be recorded in a weekly form during the treatment period to monitor participants’ compliance and safety, and adverse events will be further assessed fortnightly in the follow-up period. Participants’ opinion will be assessed at the end of first and final weeks of the intervention period.

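### Participants with a severe adverse event from the acupressure are told to leave the study, not only to stop the acupressure, so observable outcomes give way to imputed ones

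*Protocol article*

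**What the plan says.** The instruction is in the protocol article under Secondary outcome measures. After a severe adverse event from the acupressure, "the relevant participants will be asked to terminate the study and contact the researchers immediately". The text then provides for referral to a general practitioner or emergency department, investigation, and a written report to the ethics committee.

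Shortly before, the same paragraph deals with participants who take oral corticosteroids or have acupuncture for allergic rhinitis: "they will be asked to discontinue the self-administered acupressure treatment and considered as withdrawing from this study".

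The assessment schedule is general. Symptom scores are collected "at baseline and during the intervention period on a weekly basis and in the follow-up period on a fortnightly basis", and the RQLQs and relief medication scores follow the same pattern. Adverse events are recorded weekly during treatment; after that, "adverse events will be further assessed fortnightly in the follow-up period". The questionnaire on expectancy and on whether the blinding is credible is given twice: "opinion will be assessed at the end of first and final weeks of the intervention period". Under Outcome measures, the groups are to be compared "at baseline, at the end of the treatment period and at the end of the follow-up period".

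The Data analysis section promises intention to treat and includes anyone enrolled who has data from one or more treatments. For missing data it says "we will carry forward the worst possible outcomes for the missing data".

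**The concern.** Stopping the intervention and stopping data collection are different decisions. A severe event attributed to the acupressure is a good reason for the first. It is no reason for the second if the participant is willing to go on filling in forms that are self-completed anyway.

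Two things are at stake. Safety is a stated aim, and the rule ends scheduled adverse event reporting for the very people judged to have been harmed, so a later course or a later event is no longer sought on the schedule. On efficacy, the rule creates missing data by instruction, and the missing-data rule then fills the gap with a worst-case value. The Discussion presents worst-case imputation and intention to treat as the means of managing attrition bias, but here the protocol itself produces the attrition. Nothing in the article presents this as a deliberate choice to count such participants as treatment failures.

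**Working it through.** The plan states no figure of its own on this point. The check is a reading of the text followed by a count.

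**Reading.** The rule on corticosteroids and acupuncture names two consequences: stopping the acupressure and withdrawal from the study. It applies both, but it shows that the authors have words for each. The severe-event rule names only the study. Referral, investigation and the ethics report deal with the event; none of them collects scheduled outcomes. The weekly and fortnightly schedules make no provision for people told to leave.

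**Assessment points.** A 4-week intervention with weekly forms gives weeks 1, 2, 3 and 4. An 8-week follow-up with fortnightly forms gives weeks 6, 8, 10 and 12. Total: 4 + 4 = 8.

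**Comparisons.** The t-tested primary variables are "nasal and non-nasal symptom scores, QoL, global assessment score as well as the total score of the four domains", which makes 5. RQLQs (counted as one variable) and relief medication add 2, so 5 + 2 = 7 variables. There are two post-baseline time points, end of treatment (week 4) and end of follow-up (week 12), so 7 × 2 = 14 comparisons.

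**What one early stop removes**, assuming that the form for the stopping week is completed:

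| Stops at end of week | Assessments lost (of 8) | Comparisons using an imputed value (of 14) | Opinion questionnaires lost (of 2) |
|---|---|---|---|
| 1 | 3 + 4 = 7 | 14 | 1 |
| 2 | 2 + 4 = 6 | 14 | 1 |
| 3 | 1 + 4 = 5 | 14 | 1 |
| 4 | 0 + 4 = 4 | 7 | 0 |

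Stopping in weeks 1 to 3 misses both comparison points. Stopping after the week 4 form misses only the second.

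**Ceiling on the effect of one participant.** Assume that a domain score stays on the 1 to 7 scale and that all 45 planned participants in the arm are analysed. An imputed value can then differ from the true one by at most 7 − 1 = 6 points, which moves the arm mean by at most 6/45 = 0.13 points. The shift would be smaller if the worst value means the participant's own worst score, which the text leaves open. The article gives no SD, so this cannot be turned into a loss of power, and it gives no event rate, so it cannot be turned into an expected bias.

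**The case against.** The strongest reply is that this is a safety instruction to a lay person treating themselves at home, not a statement about data collection. The corticosteroid and acupuncture rule runs stopping treatment and withdrawal together, so the article may not use these terms with care, and the fuller protocol or the figures not shown may provide for continued follow-up. That weakens any inference about intent, but it does not change the words. The instruction as written is to leave the study, and a participant or site would be following it correctly by ending the forms. An analysis plan cannot recover data that the protocol told people not to provide.

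Second, the severe event itself is well covered: immediate contact, referral, investigation, a report to the ethics committee and, under Randomization and blinding, access to the allocation with documentation in the case report form. This stands. The loss is confined to later scheduled safety and outcome data.

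Third, the trigger is very narrow. Pressure is self-applied, kept comfortable and lasts 1 minute per point, and both arms use the same technique, so there is no ground for expecting events in one arm only. This also stands, and it is why the point is minor. The table above counts what one participant would lose; it does not measure harm to the trial.

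Fourth, assigning a poor outcome after a severe harm can be defended as a treatment-failure strategy. It can, but only if it is chosen and stated. Here it arises as a by-product of the missing-data rule.

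Finally, the corticosteroid and acupuncture rule loses data in the same way and may affect more people. That is a further instance of the same problem, not a reason to leave this one.

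**Conclusion.** The point holds and is minor. The article directs participants with a severe acupressure-related event out of the study, and no visible text keeps them on the scheduled forms. Each such participant would lose 4 to 7 of 8 assessments if they stop at the end of one of weeks 1 to 4, and would enter 7 or 14 of the 14 post-baseline comparisons with an imputed value. The effect on the efficacy result cannot be quantified from the document. It is probably small, and it is nil if no such event occurs. The conclusion rests on the literal wording and on the visible text alone; if the authors meant only that the acupressure should stop, the sentence still says otherwise and needs correcting.

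**What to change.** Reword the instruction so that a participant with a severe adverse event stops the self-administered acupressure and contacts the researchers at once. Add that those who are willing continue the existing adverse event, symptom, RQLQs and medication forms on the original schedule to week 12, and that their observed scores are used in the intention-to-treat analysis, with imputation only where a form is truly missing. Referral, investigation and reporting to the ethics committee stay as they are. The corticosteroid and acupuncture rule could be reworded in the same amendment.

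The cost is one sentence of amendment while recruitment is still described as in progress, with no new instruments. The downside is some form-filling for a few unwell people, who remain free to decline.

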### Data management

An individual file for each participant will be used to archive a hard copy of the case record forms including informed consent, results of the allergen skin-prick test, results of the physical examinations and all completed questionnaires. The files will be stored in the lock-up cabinet. The electronic submission documents will be kept in a RMIT University password-protected computer. Only the investigators of this study will have the authority to access the data. The results of the study and the grouping information of the participants will be provided to the individual after completion of the trial. Publications will only report aggregated data. Personal identity will not be disclosed.

### Data analysis

Statistical analyses will be performed by an independent statistician at RMIT University using IBM SPSS Statistics for Windows Version 25 software (IBM Corp., Armonk, NY, USA). The chi-square test will be used to assess differences between the two treatment groups on categorical variables such as characteristic and demographic data at baseline. The *t* test will be used to assess differences between the two treatment groups on the primary outcomes (nasal and non-nasal symptom scores, QoL, global assessment score as well as the total score of the four domains) and secondary outcome variables (RQLQs and relief medication scores) at the end of treatment and follow-up periods. All analyses will follow the intention-to-treat principle. The Worst-Case-Scenario method will be employed to deal with the missing data. That is, we will carry forward the worst possible outcomes for the missing data. Participants enrolled in the study with data from at least one treatment will be included for analysis. No interim analysis will be performed due to the short duration of the trial.

All comparisons will be two-tailed and *p* values < 0.05 will be considered as statistically significant. Subgroup analysis may be performed according to syndrome differential diagnosis of Chinese medicine, severity of symptoms or age group of participants.

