**Methods/design:**

We have designed a randomized, single-blind, non-specific controlled, two-arm, parallel clinical trial involving a 2-week run-in period, a 4-week intervention period and an 8-week follow-up period. The eligible participants will be randomized into either a specific or a non-specific acupressure group. They will be required to perform self-administered acupressure on either five specific acupressure points or five non-specific acupressure points, 1 min for each point, twice a day for 4 weeks. Participants will be asked to complete self-administered questionnaires for outcome measures including a 7-point scale of symptom severity, the Rhinoconjunctivitis Quality of Life Questionnaire with Standardized Activities (RQLQs), relief medication scores, adverse events and participants’ opinion of this study at the different assessment points throughout the trial period. Data will be analyzed by the chi-square or *t* test using Statistical Package for Social Science (SPSS) software.

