### Recruitment

People who are interested in taking part in this trial will be provided with a Participant Information Sheet with Consent Form (PIS-CF) and asked to complete a general questionnaire and screening questionnaire if they agree with the PIS-CF. Written consent will be obtained from each participant by the investigators before an initial interview. The activities in the initial interview will include the allergen skin-prick test, a physical examination and a Chinese medicine differential diagnosis [22] to achieve an AR diagnosis. The participants meeting the inclusion criteria will enter the 2-week run-in period. During this period, every participant will be asked to conduct two sets of weekly baseline assessment including a 7-point scale symptom severity assessment form [23], a Rhinoconjunctivitis Quality of Life Questionnaire with Standardized Activities (RQLQs) [24] and a medication usage form. All baseline assessment forms will be submitted in the first intervention session. Figure 1 outlines the procedures of the clinical trial.

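### The outcome tests are unadjusted t tests that leave the two run-in assessments unused; adjusting for baseline would gain precision at no cost

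*Protocol article*

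**What the plan says.** The protocol article fixes the test in two places. The Abstract (Methods/design) says "Data will be analyzed by the chi-square or" t test. The Data analysis section says the t "test will be used to assess differences between the two treatment groups on the primary outcomes", meaning the four domain scores and their total, and applies the same test to the RQLQs and relief medication scores, "at the end of treatment and follow-up periods". No covariate, ANCOVA or repeated-measures model appears anywhere.

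The data needed for adjustment are already planned. Under Recruitment, "every participant will be asked to conduct two sets of weekly baseline assessment", covering the symptom scale, the RQLQs and medication use. Primary outcome measures says the symptom domains are scored "at baseline and during the intervention period on a weekly basis and in the follow-up period on a fortnightly basis".

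The article does not say outright whether the t test is on scores or on change from baseline. Outcome measures states: "The comparison between two groups will be at baseline, at the end of the treatment period and at the end of the follow-up period". A comparison at baseline itself, listed alongside the two later ones, most naturally means raw scores at each time point.

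**The concern.** A participant's symptom score before randomization usually predicts the score afterwards. Table 1 sets no symptom-severity limit, and existing AR medication may continue, so a wide spread at entry is a reasonable expectation. Randomization and blinding describes 1:1 allocation and no stratification by severity, so no described design feature balances that spread between arms. If the outcome test ignores baseline, predictable between-person variation stays in the error term. The interval is then wider than it need be, and any chance difference between arms at entry carries through to the estimate. Comparing the arms at baseline describes such a difference but does not correct it.

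At stake are precision and the reading of a result where the arms happen to differ at entry. The validity of the test is not in question.

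**Working it through.** **Inputs from the protocol article.** Sample size: "The effect size estimate is 0.6505" and "To achieve 80% power at the significance level 0.05 we need 45 subjects per group taking into consideration a 10% dropout rate". Data analysis: two-tailed tests at 0.05. Randomization and blinding: 1:1 allocation.

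**Assumed, because the article gives no figure.** The correlation r between the baseline and end-point score is taken as 0.3, 0.5 and 0.7. The effect of 0.6505 is taken as standardized by the raw end-point SD.

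**1. The plan's own figure.** A two-sided two-sample t test (noncentral t) with d = 0.6505 and 80% power needs 39 per group, and 39/0.90 = 43.3, so 44. The normal approximation gives 38, then 43. The stated 45 is within two of both. The sample size therefore rests on the same unadjusted comparison. With 10% lost, 45 × 0.9 = 40.5, so about 40 complete cases per arm, and power is 81.9%.

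**2. Gain from adjustment, complete cases.** ANCOVA multiplies the residual variance by 1 − r², so the effective d is 0.6505/√(1 − r²). Power at 40 per arm:

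| r | Residual variance | Reduction | t test on raw scores | t test on change scores | ANCOVA |
|---|---|---|---|---|---|
| 0.3 | 0.91 | 9% | 81.9% | 68.0% | 85.4% |
| 0.5 | 0.75 | 25% | 81.9% | 81.9% | 91.3% |
| 0.7 | 0.51 | 49% | 81.9% | 96.0% | 98.0% |

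The change-score column uses a variance of 2(1 − r). It is worse than raw scores below r = 0.5, and ANCOVA is better than both at every r shown.

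**3. Using both run-in scores.** If all scores correlate equally at r, the mean of two baselines has variance (1 + r)/2, and the residual variance is 1 − r²/[(1 + r)/2]. This gives 0.862, 0.667 and 0.424 for the three values of r, with power of 87.2%, 94.0% and 99.3%.

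**4. The same comparison under the planned missing-data rule.** Data analysis fills missing values with the worst possible outcome, so steps 2 and 3 do not describe the analysis as it would be run. A simulation used 45 per arm, 10% missing at random, r = 0.5 and the worst score at an assumed 2 to 3 SD above the control mean. With the worst score at 2 SD, power is about 65% for the t test and 71% for ANCOVA. At 3 SD it is about 51% and 55% to 56%. The gain is about 4 to 7 points. The imputed values weaken the link with baseline: the observed correlation falls to about 0.40 to 0.35.

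**5. Chance imbalance.** The SE of the baseline difference at 45 per arm is √(2/45) = 0.211 SD. The mean absolute imbalance is 0.211 × √(2/π) = 0.17 SD, and the 95% limit is 1.96 × 0.211 = 0.41 SD. The unadjusted difference shifts by r times the imbalance. At r = 0.5 that is typically 0.5 × 0.17 = 0.08 SD, or 0.08/0.65, about 13% of the planned effect. At the limit it is 0.21 SD, or 32%.

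**The case against.** The strongest reply is that nothing planned is wrong. Under 1:1 randomization the t test is unbiased and holds 5% averaged over randomizations, and the sample size was calculated for that test. This stands. A reader might infer that the planned analysis is biased or underpowered by its own reckoning because it omits baseline; the documents do not support that.

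Four further points stand in whole or in part.

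- **Raw or change scores.** The article does not settle this. If change scores were meant, baseline would not be ignored, and at r = 0.7 the advantage of ANCOVA would be 2 points (96.0% against 98.0%) instead of 16. ANCOVA is still the better choice.
- **Power of 91% or more.** A reader might take this as what the trial would achieve. It needs an assumed r, complete cases, and an effect standardized by the raw end-point SD. Sample size takes the effect from an acupuncture study without saying how it was standardized, so part of the gain could be counted twice if it came from change or adjusted scores. Under the worst-case imputation at r = 0.5, 91% is not reached.
- **Imbalance of a third of the planned effect.** That is the 95% limit, not the typical case. Over repeated randomizations this variation is already in the standard error of the t test, so lost precision and exposure to imbalance are largely one cost seen from two sides.
- **Long recruitment.** Trial status gives August 2017 to June 2020. Entry over several seasons may widen baseline spread, but symptoms that change between run-in and end-point could also lower r.

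It would also be too strong to say that every outcome has a baseline. Recruitment lists only the symptom scale, RQLQs and medication use. Adverse events and participants' opinion are first recorded during treatment.

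The defence that an article leaves such detail to the analysis plan does not carry far, because this one names the test in both the Abstract and the Data analysis section.

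**Conclusion.** The point holds as a free improvement in efficiency, not as an error of validity. The named test leaves unused the two pre-randomization assessments of the three measures it is applied to, and a baseline-adjusted analysis is at least as good in every case checked. For r between 0.3 and 0.7, residual variance falls by 9% to 49%. Complete-case power at d = 0.6505 rises from 82% to between 85% and 98%. Under the plan's own worst-case imputation with 10% missing, the gain at r = 0.5 is about 4 to 7 points. A typical chance imbalance moves the unadjusted difference by about 0.08 SD at r = 0.5, with a 95% limit of 0.21 SD. These sizes depend on r, on how 0.6505 was standardized and on where the worst score lies, none of which the article gives. The direction of the gain does not depend on the particular values.

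**What to change.** In Data analysis, and in the matching sentence of the Abstract, replace the t test for the symptom scores, RQLQs and medication scores by ANCOVA, with the mean of the two run-in assessments of the same score as covariate. Fit it at each planned time point, and name one of them as primary (the end of treatment or another single time point), since the article tests two and designates neither. Report the adjusted difference with its 95% confidence interval. State that the outcome is the score itself, which removes the doubt about change scores.

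The cost is a dated change of wording before unblinding. No new data, visits or participants are needed, SPSS fits the model, and 45 per group need not change.
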